#### Costs items

In addition to change in primary outcomes, the costs of Multisystemic Therapy compared to CAU will be assessed. Cost assessment will be done from a societal perspective, over a time horizon of one year.

Cost components of adolescent antisocial behaviour will be measured by a modified version of the Trimbos/iMTA questionnaire for Costs associated with Psychiatric Illness (TiC-P) [24]. This questionnaire is originally designed to measure direct and indirect costs of mental health problems. For the current study, we adjusted the questionnaire to a version more suitable for assessments of costs related to child antisocial behaviour [25]. We did this mainly by adding items about youth and social care. Direct costs of the interventions as well as indirect costs will be assessed via various informants, namely professionals, parents and adolescents.

*Direct costs* concern use of all resources that is directly related to the intervention and will be estimated through the review of (time) investment of the professionals, including training, overhead, communication with relevant others, and time and travel costs of professionals involved. In addition, direct costs of health and youth care utilization will be assessed via parents (among other things: visits of the adolescent and parent to health and youth care professionals, hospitalizations and residential treatments, contact with judicial authorities and medication use).

*Indirect costs* are characterized as productivity losses, due to time lost from work because of the antisocial behaviour of the adolescent [26]. Data on productivity loss will be collected via the Short Form Health and Labour Questionnaire (SF-HLQ) that is part of the TiC-P [24]. The Short-Form HLQ (SF-HLQ) contains questions about absence from work, reduced efficiency at work and difficulties with job performance.

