## Background

The direct costs associated with antisocial and delinquent behaviour of adolescents are high. Estimated expenses of incarceration amounted to 114.000 - 250.000 euro per youth per year [1,2]. The degree of recidivism among juveniles who were incarcerated has been estimated to be at least 75% in the first three years after release [3]. Besides direct costs of locking up offenders, incarceration also has wider costs and consequences. Indirect costs include amongst other things extra support for the adolescent to reintegrate into the education system or the labour market and lost wages of parents due to the high time demands of an incarcerated child [1].

As a result of the unfavourable outcomes of incarceration, there is a strong need for evidence-based treatments that can provide an alternative to incarceration for youth with serious emotional and behavioural problems. Multisystemic Therapy (MST) has been proposed as a promising, cost-effective intervention for this group of young people. Several studies show significant reductions in number of serious crimes and days incarcerated [4-6]. However, research conducted in Canada and Sweden did not show significant differences in treatment effects between MST and care-as-usual (CAU) [7,8]. A review by Littell et al. [9] confirmed that the evidence regarding the superiority of MST compared to CAU is still inconclusive.

The introduction of an intensive family- and community-based treatment such as MST will always be associated with additional costs. Cost-effectiveness studies in child and youth care are required to provide decision makers with information on whether this intervention represents good value for money. Therefore, studies are needed that assess how well MST works – its influence on behaviour and the use of health and welfare services – and how much it costs. Cost-effectiveness analysis (CEA) is an approach that combines these requirements.

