#### Primary outcomes

Primary outcomes of this study include: recidivism and the frequency and seriousness of antisocial behaviour and other types of problems (internalizing problems, substance use). *Recidivism* will be assessed with data of the Research and Policy Database for Judicial Documentation. With this data we will assess the number of arrests, type and severity of offence of adolescents re-offending during the research period.

*Prevalence and seriousness of antisocial behaviour* will be assessed via different informants and instruments. First, parents and adolescents are asked to fill in the 33 items of the Delinquent Behaviour scale and the Aggressive Behaviour scale of the Child Behaviour Checklist (CBCL: 33 items) [19] and the Youth Self Report (YSR: 30 items) [20,21] respectively. For each item, the child’s behaviour has to be rated on a three-point scale, ranging from 0 (never) to 2 (often).

Additionally, adolescents will fill in two subscales of the Self-Report Delinquency scale (SRD) were used to assess self-report delinquency [22]. Adolescents will be asked to indicate on a list of potential delinquent behaviours whether they engaged in the described behaviours during the past 6 months (‘yes’ or ‘no’). The SRD ‘Violent offending’ (5 items) and ‘Property offences’ (10 items) scales will be used.

*Other types of problems* of the adolescent firstly comprise anxiety/depression, withdrawal and somatic complaints. These items will be measured with 25 items of the Youth Self Report [20,21].

In addition substance use (use of alcohol, soft and hard drugs) will be measured with several questions from a Dutch questionnaire used in the study Youth and risky behaviour [23].

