### Strengths and limitations

This study will contribute to the extension of scientific knowledge about economic evaluation in the field of child and youth care. This concerns the evaluation of the actual balance between costs and effects in a field of care where this has hardly ever been explored before, i.e. with very limited sources to derive costs of other outcome valuations from. The study will be conducted as part of a randomized controlled trial. By using such a design, it can be assumed that any confounding variables are cancelled out.

Furthermore, the study will be conducted as a multicentre trial. This will increase the generalizability of the study because this will lead to a large number of participants, different geographic locations and the ability to compare results among organizations. We will obtain both direct and indirect costs across the entire field of youth care. We will also include quality of life measures. To increase inclusion and prevent loss to follow up, all adolescents and parents will receive assistance in administering the questionnaires. Finally, most outcome variables will be assessed via two informants. Multi-informant assessment is recommended as a way to obtain a more complete picture of the adolescent than reliance on self- or parent-report alone [16].

Despite the strengths and innovative aspects of this cost-effectiveness study, there are some issues that our study is unable to take into account. First, follow-up is limited to a period of six months. To determine long-term effects of the intervention, there should be follow-up after a couple of years to assess the effects and costs when the adolescent is older. Second, it is to be expected that we will be dealing with a ‘difficult-to-reach”-population.

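### The costs and the ICER numerator are called societal, but no defined cost class can hold victim losses, and the offences taken from the judicial register are not carried into the costing

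*Protocol article*

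**What the plan says.** The Costs items section sets the perspective and horizon: "Cost assessment will be done from a societal perspective, over a time horizon of one year". It then defines what is counted.

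- **Direct costs, first part.** These concern "use of all resources that is directly related to the intervention and will be estimated through the review of (time) investment of the professionals", with training, overhead, communication and travel included.
- **Direct costs, second part.** The "direct costs of health and youth care utilization will be assessed via parents (among other things: visits of the adolescent and parent" to professionals, and then "hospitalizations and residential treatments, contact with judicial authorities and medication use").
- **Indirect costs.** These "are characterized as productivity losses, due to time lost from work because of the antisocial behaviour of the adolescent".

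The same section says that the cost questionnaire (TiC-P) was adapted mainly with youth and social care items. Unit prices and cost calculations takes unit costs from Dutch guideline prices and names no price for an offence.

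Under Primary outcomes, recidivism comes from a judicial database: "we will assess the number of arrests, type and severity of offence of adolescents re-offending during the research period". The Statistical analysis section divides incremental societal costs by incremental effects at 12 months. The effects are aggressive and delinquent behaviour in the cost-effectiveness analysis and EQ-5D utilities in the cost-utility analysis. Strengths and limitations describes the scope in these words: "We will obtain both direct and indirect costs across the entire field of youth care". Its list of limitations does not mention costs of crime.

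**The concern.** A societal perspective tells the reader that costs are counted whoever bears them. In a trial of adolescents selected for serious, violent and chronic antisocial behaviour, victims are an obvious group that bears cost. The Background reports that several earlier studies of MST found fewer serious crimes and fewer days incarcerated. The article also criticises earlier economic studies for incomplete costing and names judicial authorities among its intended users.

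If offence costs borne by victims stay outside the numerator, a difference between arms in offending does not show up there. The incremental cost would still carry the societal label, and a policy maker would have no signal that it is incomplete.

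**Working it through.** The article states no figure for offence costs, so there is nothing to reproduce. The check compares the cost classes with the label and then works out the direction and possible size of the gap.

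**Step 1. Where could an offence cost sit?**

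| Cost of an offence | Intervention resources | Health and youth care use, via parents | Productivity loss |
|---|---|---|---|
| Victim loss, property damage | no | no: not care used by the adolescent or parent | no: the class is work time lost because of the adolescent's behaviour, collected with the SF-HLQ |
| Police and court response | no | partly: contact with judicial authorities | no |
| Detention | no | possibly: residential treatments, judicial contact; the list is open | no |

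The first row has no home. The open wording of the second direct-cost class does not change this, because it extends care utilisation and a third party's loss is not care utilisation.

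**Step 2. Where do register offences enter the ratios?** The article uses them as a recidivism outcome and never says that they are priced. The effect in the cost-effectiveness ratio is the aggressive and delinquent behaviour scores. These reflect offending indirectly, through parent and adolescent report. The effect in the cost-utility ratio is the EQ-5D utility, which has no dimension for offending. In that ratio, victim losses are in neither the numerator nor the denominator.

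**Step 3. Direction.** Let ΔO be mean offences per youth-year in MST minus CAU, and u the cost per offence that no planned class captures. Then

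planned ΔC = full ΔC − u × ΔO.

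If MST has fewer offences (ΔO < 0), the planned difference is too high by u × |ΔO|, which counts against MST. If CAU has fewer, it is too low by the same rule, which counts against CAU. If ΔO = 0, the gap does not affect the difference.

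**Step 4. Possible size.** Neither u nor ΔO is in the article, so both are assumed here. The entries are |ΔO| × u in € per youth.

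| Difference in offences per youth-year | u = €500 | u = €2,500 | u = €10,000 |
|---|---|---|---|
| 0.1 | 50 | 250 | 1,000 |
| 0.5 | 250 | 1,250 | 5,000 |
| 1.0 | 500 | 2,500 | 10,000 |

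**Step 5. What the article's own price covers.** The Background gives one relevant figure: "Estimated expenses of incarceration amounted to 114.000 - 250.000 euro per youth per year". Per day this is 114,000/365 = €312 to 250,000/365 = €685. It prices detention, which the planned classes may already capture in part, so it cannot be used to size the gap in victim costs.

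**The case against.** The strongest reply has four parts.

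- **Justice costs are listed.** Contact with judicial authorities and residential treatments are direct costs in an open list, and the modified questionnaire is not shown. This stands. A reader might infer that detention, police and court costs are left out altogether, but the article does not support that. Not being named in an open list is not exclusion, and a condensed article may leave such items to the instrument.
- **Materiality is not demonstrated.** This also stands. A reader might infer that the ICER misses the largest component, or the main saving or loss from MST. No figure in the article ranks victim costs against any other cost. The Background also cites studies in Canada and Sweden with no significant difference in treatment effect between MST and usual care, so a difference in offending is not established.
- **Offending is already in the effect.** This is true in part for the cost-effectiveness ratio, where delinquent behaviour is an effect measure. Pricing offences in the numerator of that ratio partly counts one change twice, and the report should say so. The reply does not reach the cost-utility ratio.
- **The choice of items is a design decision, and the youth care sentence under Strengths only describes breadth.** Both are fair. But the article states the perspective and defines the classes itself, and it does not refer cost scope to another document. The mismatch between label and content therefore does not come from condensation.

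**Conclusion.** The point holds in a limited form. Followed as written, the plan yields a numerator narrower than the term societal: victim losses and property damage have no cost class, and the register offences are not carried into the costing. The limitations do not acknowledge this.

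Any bias is conditional on a difference in offending between the arms, and it runs against the arm with fewer offences. It is clearest in the cost-utility ratio. Its size cannot be derived from the article. The €50 to €10,000 per youth rests entirely on assumed offence differences and unit costs and shows only that the gap could range from negligible to material. Omission of detention is not shown.

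**What to change.** Keep the planned costing and add one analysis.

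1. Price the register offences by type over the one-year horizon. Include victim costs. Include police and court costs only where parent-reported judicial contact does not already cover them.
2. Report cost differences, ICERs and acceptability curves with and without this class.
3. State that in the cost-effectiveness analysis the delinquent behaviour effect already partly reflects offending, so the version with offence costs overlaps with the denominator.

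If the sponsor does not price offences, qualify the perspective under Costs items and Statistical analysis, for example as health care, youth care, judicial contact and productivity. Also add the exclusion of victim costs to Strengths and limitations.

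The first option needs unit prices by offence type, a rule for overlap with judicial contact, and one further run of the bootstrap. The offence data are already collected and the questionnaire need not change. Its drawback is that unit costs per offence are uncertain, which is the reason for showing both versions. The second option costs only the rewording.

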#### Unit prices and cost calculations

Estimates of unit costs will be based on the Dutch guideline prices [25]. Costs of medication use will be based on the listed prices, including value added tax, and a pharmacists allowance. Costs due to productivity losses will be based on the overall mean hour productivity cost for men and women, calculated according to the human capital approach [27]. Multiplying the respective volumes of resource use with their corresponding unit prices will result in the associated total costs. Costs will be calculated in the European currency (Euro). The price level used will be of 2011.

*Quality of life* will be assessed with the EuroQol (EQ-5D) and the Short Form-20 (SF-20), which are validated tools for measuring general health-related quality of life [28,29]. The EQ-5D is a self-administered, generic, health-related quality-of-life questionnaire that contains two sections, a descriptive section and a valuation section. The *descriptive* section consists of five dimensions: mobility, self-care, usual activities, pain/discomfort and anxiety/depression. Each dimension has three levels of severity: no problems, some/moderate problems, and extreme problems. For each severity level a valuation is available that is based on the judgment of the general public about the value of this health state. Values on the five dimensions will be transformed into one single score by applying a formula, ranging from 0 to 1 (with lower scores representing more problems), and by using the British tariff [30]. We will use the British tariff because this is used by default in Europe, and thus the results are more generalizable and the comparison between studies is more adequate.

The *valuation* section of the EQ-5D contains a visual analogue scale, on which the participant rates his/her health on a vertical, visual analogue scale where the endpoints are labelled ‘Best imaginable health state (score of 100)’ and ‘Worst imaginable health state (score of 0)’. Valuations of the VAS (original values 0–100) will be linearly transformed into a 0 to 1 score. This valuation of health status is a so-called ‘utility’, a relative valuation of a health condition compared with perfect health and dead. This method has been found to be efficient and easy to use, and appears to provide meaningful values for relative preferences of health and treatment [31]. Thus far the EQ5D has not been validated in the domain of behavioural problems, i.e. there are no formal utilities available for severe antisocial behaviour. In a separate study we have generated valuations for serious behaviour problems in children and adolescents ([name] et al., submitted).

The *SF-20* assesses six important health concepts: physical functioning, role functioning, social functioning, mental health, current health perceptions, and pain. Each dimension has five levels. For each subscale, a scale score will be calculated. The scale scores can be seen as multidimensional, health-related quality of life indicator. The internal consistency of the subscales of the Dutch SF-20 has proved sufficiently high: Cronbach's alpha for each subscale was at least .80 [32,33].

### Data collection procedure

Data will be collected using a standardized self-report questionnaire in a face-to-face situation. The questionnaires will be administered before the intervention (T1), directly after the intervention (T2) and six months after the intervention (T3). Adolescents and their parents will both receive €10 for filling out the questionnaire. The therapist will fill out a questionnaire after the treatment has finished (T2). The questionnaires are also available in old Berber for the Berber Moroccan families. In addition, we make use of one Arab translator who will visit all Arab families.

### Sample size

Sample size will be based on testing differences in outcomes between MST and CAU, at .80 power, an alpha of .05 and a medium effect size [34]. This leads to 64 participants per group. It should be noted that the power to detect a difference in costs and/or other outcomes is extremely difficult to assess a priori. Since this is a first attempt to perform a cost-effectiveness study in this area and no pilot data are available (allowing an assessment of variability) we cannot present a formal power calculation. However, to determine a clinically relevant effect size of 0.5 with a power of 80% at an alpha of 0.05, we will need 81 in each treatment arm, making 2 × 100 a probably safe sample size [35].

### Statistical analysis

First, descriptive statistics will be performed to describe the demographic characteristics of the study population.

Second, primary measures of effect will be analysed using within group comparisons (pre-post treatment) and between group comparisons. The latter one will use difference scores (pre-post intervention) after which the treatment effects of the two treatment conditions will be compared. Statistical testing will be done using either the paired t-test or the Wilcoxon signed-rank test for comparisons within the treatment groups and the unpaired t-test or the Mann–Whitney U test for comparisons between the treatment groups.

Third we will describe the mean costs per respondent in both treatment groups. Differences in costs between the intervention group and the control group will presented based on the trial data, and 95% confidence intervals will computed based on bootstrap re-sampling with 5000 replications of the trial data. Separate estimates will be made for different cost categories. For the cost-effectiveness analysis, mean annual societal costs will be linked to the primary measure of effect (Aggressive behaviour and Delinquent behaviour). A cost utility analysis will link the EQ-5d based utilities to the cost.

Fourth, point estimates for the incremental cost-effectiveness and cost utility ratio (ICER) will be computed on complete cost-effect pairs by dividing the incremental societal costs by the incremental effects at 12 months. Uncertainty around the ICERs will be estimated using bootstrapping, generating 5000 replications of the original dataset. A cost-effectiveness acceptability curve (CEAC) will be generated to represent the probability that MST is cost-effective compared to usual care over a range of thresholds [26,36].

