### Recruitment

Participants will be recruited via three MST institutions spread over the Netherlands. The recruitment per organization will differ because of differences in the setting in which MST will be delivered. One MST organization is located in the North of the Netherlands; the other two locations are in the West of the Netherlands.

In *the North of the Netherlands*, the study population will consist of adolescents referred by family guardians of the Youth Care Office to the youth care program called “Do What Works”. This program consists of maximum six weeks secure residential care, followed by MST (Intervention) or FFT (Functional Family Therapy; Care-As-Usual). After the residential period, adolescents will be randomized to MST or to Care-As-Usual. At the same time, adolescents and their parents will be informed about the MST-effectiveness study and they will be asked for their informed consent. Upon mutual consent of the adolescent and the parents, a first appointment will be made before the start of MST or Care-As-Usual, in order to obtain written informed consent and to administer the first questionnaire.

The recruitment in *the Western part of the Netherlands* will be conducted via referring agencies such as Child Protection Council, juvenile judges, Bureaus Youth Care and local referral institutions. The referrers will inform the potential eligible juveniles and their families that a study will be conducted to investigate the effectiveness of youth care. If the families meet the inclusion criteria for MST according to the MST supervisors of the participating institutions, research procedures will be explained to the juveniles and their families, and their informed consent to participate in the study will be obtained by researchers.

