### Participants

Participants eligible for this study are adolescents (and their families) between 12 and 18 years old who show serious, violent, and chronic antisocial behaviour. Exclusion criteria are an IQ below 70, acute psychiatric problems that place adolescents and their family at risk for out-of-home placement, and dominant sexual problems. Adolescents may be court-ordered or referred by primary health care, social workers or self-referred.

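### Within-arm pre-post significance tests are planned as an analysis of the primary measures of effect, although they cannot separate a treatment effect from change that would occur anyway

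*Protocol article*

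**What the plan says.** The Statistical analysis section of the protocol article sets out the effect analysis in one sentence: "primary measures of effect will be analysed using within group comparisons (pre-post treatment) and between group comparisons". It then assigns "either the paired t-test or the Wilcoxon signed-rank test for comparisons within the treatment groups", and the unpaired t-test or Mann-Whitney U test on difference scores to the comparison between arms. The two kinds of comparison stand side by side and neither is ranked above the other. The only analysis called descriptive concerns the demographic characteristics.

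The sentence on difference scores continues "after which the treatment effects of the two treatment conditions will be compared", which reads as if the change inside each condition were already that condition's treatment effect.

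The Participants section describes eligible adolescents as those "who show serious, violent, and chronic antisocial behaviour". The Abstract places T2 five months after T1. The Sample size section bases the numbers on the difference between MST and CAU, and the ratios in the Statistical analysis section use incremental costs and effects.

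**The concern.** The trial asks whether MST does better than CAU, and randomisation protects that comparison only. A paired test within one arm has no randomised control. It asks whether the mean score moved between T1 and T2, whatever the cause. Among adolescents who enter because their behaviour is serious, some movement without any treatment effect is plausible, for example regression to the mean or maturation. The article does not discuss either one, so this is general reasoning and not something the documents report.

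If the within-arm tests are reported as analyses of effect, two wrong messages become possible when MST and CAU do not differ. One is that both treatments work, because both arms improved significantly. The other is that MST works and CAU does not, because only the MST arm crossed the significance threshold. The article says that its results are meant to inform policy makers, who may well read a pair of p-values in this way.

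**Working it through.** **Inputs from the article.** Alpha 0.05 (taken as two-sided, since the article does not say), power 0.80, medium effect size 0.5, 64 per group, target 100 per arm, 1:1 allocation.

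**Inputs assumed.** The article gives neither a pre-post correlation nor an expected change without a treatment effect. I take a correlation r of 0.6 (range 0.5 to 0.7) and a change d, common to both arms, of 0.1 to 0.3 baseline SD. SDs are taken as equal at T1 and T2. The true MST-CAU difference is set to zero.

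**The plan's own figure.** A two-sample t-test with effect size 0.5, two-sided alpha 0.05 and power 0.80 needs 63.8, so 64 per group. The stated 64 reproduces, and it is a between-arm calculation.

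**Within-arm test.** The SD of the change is SD × √(2(1 − r)), so the standardised change is dz = d / √(2(1 − r)). With r = 0.6 the divisor is √0.8 = 0.894. The power of the paired t-test comes from the noncentral t distribution with n − 1 degrees of freedom and noncentrality dz × √n.

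- d = 0.2, n = 100: dz = 0.2 / 0.894 = 0.224, noncentrality 2.24, power 0.60.
- d = 0.3, n = 100: dz = 0.3 / 0.894 = 0.335, noncentrality 3.35, power 0.91.
- d = 0.3, n = 64: noncentrality 0.335 × 8 = 2.68, power 0.75.

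**Patterns across the two arms.** The arms are independent, so the probabilities multiply.

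| Shared fall, n per arm | Each arm significant | Both significant | MST only |
|---|---|---|---|
| 0.2 SD, 100 | 0.60 | 0.60² = 0.36 | 0.60 × 0.40 = 0.24 |
| 0.3 SD, 100 | 0.91 | 0.913² = 0.83 | 0.913 × 0.087 = 0.08 |
| 0.3 SD, 64 | 0.75 | 0.752² = 0.57 | 0.752 × 0.248 = 0.19 |

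**Sensitivity to r (0.5 to 0.7), 100 per arm.** Each arm is significant with probability 0.17 to 0.25 for a shared change of 0.1 SD, 0.51 to 0.73 for 0.2 SD, and 0.84 to 0.97 for 0.3 SD.

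**Between-arm test.** The expected difference in change scores is d − d = 0, so any shared change cancels. A simulation of 20,000 trials (r = 0.5, d = 0.3, 100 per arm) rejected in 5.1%, in line with the nominal 5%. In the same runs each within-arm test rejected in about 84%.

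**The case against.** The strongest reply is that the valid comparison is already in the plan. The same sentence that announces the within-arm tests also announces the between-group comparison. The sample size rests on the MST-CAU difference, and the cost-effectiveness ratios, their bootstrap and the acceptability curve are all incremental. Nowhere does the article say that MST will be judged superior from two within-arm p-values, and naming those tests first is word order, not rank. All of this stands, and it limits the consequence.

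It does not remove the point. The within-arm tests are a stated analysis of the primary measures of effect, not a detail left to a fuller document, and nothing bars an effect claim from them.

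A reader might go further in four ways that the documents do not support.

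- *The Northern run-in makes both arms look effective.* In the North, "After the residential period, adolescents will be randomized to MST or to Care-As-Usual", and T1 follows. Secure care may already have lowered T1, which would tend to hide improvement.
- *Exposure in the self-report delinquency window differs by 26/20 = 1.3 in the North.* This does not fit T2 at five months (about 21.7 weeks) after T1. The six-month window at T2 reaches about 4.3 weeks back before T1. If T1 directly follows discharge, those weeks fall in the secure stay, and the ratio is about 21.7/20, or 1.08.
- *Discordant arms occur in about half of trials.* At 0.2 SD, 2 × 0.60 × 0.40 = 0.48 counts both directions and lies near the maximum of 0.50. The misleading pattern in favour of MST is 0.24, and it falls to 0.08 at 0.3 SD.
- *Referral happens at a peak of problems.* The article says chronic and sets no score threshold for entry.

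**Conclusion.** The concern holds in a limited form. The article plans within-arm significance tests as an analysis of the primary measures of effect and does not mark them as descriptive. When MST and CAU do not differ, a modest shared fall of 0.2 to 0.3 SD would make each arm significant with probability about 0.60 to 0.91 at 100 per arm, while the between-arm test stays at 5%. These figures rest on the assumed correlation of 0.6 and on the assumed size of the shared change. A shared change of 0.1 SD gives much lower probabilities, and no shared change gives 5%.

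The planned between-group test and the incremental cost-effectiveness ratios are not affected. A reader might infer that the trial's main conclusion is compromised, but the documents do not support that. What is at risk is any statement that MST, CAU or both are effective because scores changed within the arm.

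**What to change.** In the Statistical analysis section, report T1, T2 and T3 values and the within-arm change by arm descriptively. Drop the paired t-test and Wilcoxon signed-rank test as tests of effect. State that every conclusion about effect rests on the randomised between-arm contrast, and keep the term treatment effect for that contrast.

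The cost is an edit of one or two sentences and the loss of within-arm p-values. No extra data are needed, and the power of the randomised comparison does not change.
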